### Outcomes

**Primary Outcome: Preservation of Residual Kidney Function**
Time to anuria, defined as urine volume ≤100 ml/day or ≤200 ml in the short inter-dialytic period confirmed by a further collection after 2 weeks to exclude temporary illness.

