### Participant timeline

Trial entry for all participants is at the point of commencing centre-based haemodialysis as an outpatient, see Fig. 1. At this point trial eligibility will be confirmed, followed by randomization. All participants will be followed up until study completion or withdrawal because of death, transplantation, stopping dialysis (e.g. recovery of function) or patient choice, including any period after they reach the primary outcome so that the health economic analysis can be completed. The schedule of trial assessments is shown in Table 1.

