### Sample size

#### Primary outcome (time to anuria)

It can be determined from cohort studies and data collection from a large dialysis unit of 615 patients that the proportion of incident centre-based HD patients anuric by 10 months is in the region of 30% (range 25–67%) [26–30]. Sample size is based on a cumulative 10-month incidence of anuria of 30% in the control group and 20% in the treatment group and 11% competing risks (based on death and transplantation data extrapolated from the 2013 UKRR report [31]). Assuming exponential decline, proportional hazards, 90% power and 5% two-tailed significance, 185 events are required to detect the corresponding hazard ratio, with 12 months accrual and 12 months follow-up. This will require a total of 516 patients to be randomized 1:1, allowing for a 5% loss to follow-up.

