#### Primary outcome

Time to anuria will be analysed on an intention-to-treat basis (as the primary analysis) and on an as-treated basis (as the secondary analysis) using competing risks survival analysis [32], to estimate the relative risk (as expressed by the sub-hazard ratio) of the outcome (anuria) in patients where BI is used compared to control patients, accounting for the competing risks (death, transplantation). Patients undergoing modality change or recovery will be censored at the point of treatment switch. The analysis will control for known baseline covariates affecting residual function [26, 29], i.e. age, race, sex, comorbidities (separately or using a validated scoring system), antihypertensive drug use (ACE inhibitors/ARBs, calcium antagonists) and diuretic use.

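### The primary analysis censors recovery of kidney function instead of treating it as a competing event alongside death and transplantation; modality change is also censored although follow-up is not stated to end there

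*Protocol article*

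**What the plan says.** All references are to the protocol article.

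- **Statistical methods, Primary outcome.** "Time to anuria will be analysed on an intention-to-treat basis (as the primary analysis"), with an as-treated analysis as secondary. Both use a competing-risks model that reports a sub-hazard ratio, "accounting for the competing risks (death, transplantation"). The next sentence reads: "Patients undergoing modality change or recovery will be censored at the point of treatment switch". Nothing limits that sentence to the as-treated analysis.
- **Participant timeline.** "All participants will be followed up until study completion or withdrawal because of death, transplantation, stopping dialysis (e.g. recovery of function) or patient choice". Recovery therefore ends follow-up, in the same list as death and transplantation. Modality change is not in the list.
- **Outcomes.** "Time to anuria, defined as urine volume ≤100 ml/day or ≤200 ml in the short inter-dialytic period", confirmed by a second collection. The first limb is a daily volume and does not need an inter-dialytic interval.
- **Sample size.** 30% versus 20% anuria at 10 months, 11% competing risks from death and transplantation, and 5% loss to follow-up. There is no separate allowance for recovery or modality change.

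**The concern.** Three events that end follow-up are handled in two ways. In a sub-hazard model, a patient who dies or is transplanted is counted as never reaching anuria. A patient who is censored is assumed to go on to anuria at the rate of those still under observation. For someone with enough kidney function to stop dialysis, that assumption is implausible. Recovery lies at the far end of the scale that this trial measures, so the censoring is informative.

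Two things are at stake. The cumulative incidence of anuria is overstated in any arm where recoveries occur. And if the arms differ in recovery, the primary sub-hazard ratio shifts against the arm with more of it, because that arm's most favourable courses stop being credited at recovery.

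Modality change raises a separate and weaker question. The patient still has a measurable urine volume and the article does not end follow-up. Stopping the primary analysis at a post-randomisation switch departs from a treatment-policy reading of intention-to-treat.

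**Working it through.** **1. Reproduce the plan's figures.** Inputs from Sample size: 10-month incidence of anuria 0.30 and 0.20, competing events 0.11 in each arm, two-sided 5%, 90% power, 12 months' accrual plus 12 months' follow-up, 5% loss.

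With constant hazards, the total hazard is −ln(1 − p − q)/10, and the anuria share is p/(p + q).
- Control: −ln(0.59)/10 × 0.30/0.41 = 0.03861 per month.
- Intervention: −ln(0.69)/10 × 0.20/0.31 = 0.02394 per month.
- Hazard ratio: 0.02394/0.03861 = 0.620.
- Events (Schoenfeld): 4(1.960 + 1.282)²/(ln 0.620)² = 184.02, rounded up to **185**.
- Probability of an anuria event under uniform accrual: (λ/L)[1 − (e^(−12L) − e^(−24L))/(12L)], where λ is the anuria hazard and L the total hazard. This gives 0.4439 and 0.3116, mean 0.3777.
- Patients: 185/0.3777 = 489.7; divided by 0.95 = 515.5, i.e. **516**.

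Both figures are reproduced.

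**2. Events and power if recovery or switching adds further censoring.** The article gives no rates, so these are assumed. Add an exit hazard −ln(1 − x)/12 to L. Expected events are 516 × 0.95 × the mean event probability.

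| Exit per year (assumed) | Events | Power |
|---|---|---|
| 0% | 185.2 | 90.2% |
| 2% | 182.7 | 89.8% |
| 5% | 179.1 | 89.2% |
| 10% | 173.0 | 88.2% |

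The loss is 0.4 to 2.0 points.

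**3. Cumulative incidence.** Suppose the control arm shows 30% at 10 months when recovery is censored, and that recovered patients do not become anuric. With recovery hazard r as a third cause, the incidence is (λ/L)(1 − e^(−10L)), with r included in L. For recovery of 2%, 5% and 8% per year this gives 29.8%, 29.4% and 29.1%. Censoring overstates the figure by 0.2 to 0.9 percentage points.

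**4. Sub-hazard ratio.** Large-sample simulation with 400,000 patients, the hazards of step 1, and administrative censoring uniform between 12 and 24 months. Strong dependence on prognosis is modelled as follows: half the patients have 0.3 times the anuria hazard and twice the exit rate; the other half have 1.7 times the anuria hazard and no exits. *Followed on* ignores the exit and continues observation.

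| Exit per year, control / intervention (assumed) | Censored | Competing event | Followed on |
|---|---|---|---|
| 5% / 5% | 0.670 | 0.672 | 0.671 |
| 2% / 8% | 0.683 | 0.655 | 0.666 |
| 2% / 8%, no true effect on the anuria hazard | 1.028 | 0.983 | 1.003 |

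Monte Carlo error is about 0.005 for each ratio; within a row, the three analyses use the same simulated patients.

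**5. Scale.** For 2% versus 8%, the shift on the log scale is ln(0.683/0.655) = 0.042. With 185 events, the standard error of the log ratio is about 2/√185 = 0.147, so the shift is about 0.28 of a standard error.

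**The case against.** The strongest reply has four parts.

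- **No rates.** The article does not say that bioimpedance guidance promotes recovery. Entrants start maintenance dialysis for stage 5 disease, and unplanned starters are approached only once long-term dialysis is judged necessary. A large difference in recovery between arms is therefore an assumption. This stands. With equal rates the three analyses agree to about 0.002 despite strong dependence on prognosis. Any shift from extra recovery in the intervention arm is towards the null, so the rule would not create a benefit in that case.
- **Intention-to-treat.** A reader might infer that the rule contradicts intention-to-treat outright and throws away the best outcomes. The article does not support that. Patients stay in their randomised arm and contribute event-free time up to the switch. For recovery, Participant timeline ends follow-up, so no later urine data are planned. The fault there is the informative censoring.
- **Modality change.** The Aim concerns centre-based haemodialysis, planned transfer within 6 months is an exclusion, and Table 1 places all visits at routine dialysis sessions. Continued follow-up could serve the economic analysis alone. This makes censoring at the switch a defensible question, and nothing in the article shows that switching is informative. It remains true that follow-up is not ended there, so an as-randomised analysis of available data is the closer match to the label used.
- **The competing-event analysis has a different estimand.** It credits an arm for recovery itself, as the 0.983 with no true effect on the anuria hazard shows. That is a reason to retain the censored version as a sensitivity analysis. It does not justify assuming that recovered patients become anuric at the rate of those on dialysis.

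Sensitivity analyses may already be in the unseen SAP, and their absence here is not a criticism. The censoring rule, however, is stated in the article itself.

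**Conclusion.** The point holds for recovery. The article fixes a rule that separates recovery from death and transplantation without a reason, and the assumption behind the censoring is implausible. The direction is clear: incidence is overstated, and the sub-hazard ratio moves against an arm with more recovery. The size is not known. It is negligible if recovery is equal by arm, and about 0.03 on the sub-hazard ratio under an assumed 2% versus 8% per year with strong dependence on prognosis.

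For modality change the point is weaker. It rests on the mismatch between the stated end of follow-up and the censoring rule, not on demonstrated bias.

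A reader might also infer that the trial is underpowered because these exits are not budgeted, or that the primary result is bound to be materially biased. Neither follows: the power loss is at most about 2 points for exits up to 10% per year, and material bias needs differences between arms that the article neither gives nor excludes. Severity: moderate.

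**What to change.** In Statistical methods, Primary outcome, replace the censoring sentence with separate rules:

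1. Recovery of kidney function, with dialysis stopped, is a competing event together with death and transplantation. Censoring at recovery is kept as a sensitivity analysis.
2. After a modality change, patients are analysed as randomised, using urine volumes obtained after the switch where available. Censoring at the switch is kept as a sensitivity analysis.

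The first change costs one sentence. The second needs some collection logistics outside centre dialysis sessions for those who switch. Neither changes the sample size. Both should be settled before unblinding, because they define the primary estimate.

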**Fig. 1 Fig1:**
[figure not shown]
Schema for BISTRO Trial

**Table 1 Tab1:** Schedule of visits and procedures

	VISITS (Months) All undertaken at routine dialysis sessions						Urine Collections	Trial completion	Event based
Procedure	Visit −1	BaselineVisit 0	Visit 1	Visit 2	Visit 3	Visits 4–11 At 6,9,12,15,18,21,24 Months.	At 5,7,9,11,13,15,17,19,21,23,24 months. includes extra 2 weeks after primary endpoint is reached		
Eligibility	x								
Consent	x								
Residual kidney function tests for normalized GFR (urine volume and urine + blood to lab)	x		x	x	x		x		
Height (cm)	x								
Web-based randomisation		x							
Date of birth		x							
Ethnicity		x							
Sex		x							
Full medication list		x							
Primary Renal Disease Diagnosis		x							
Stoke comorbidity score		x							
Renal Registry comorbidity fields		x							
Planned/unplanned start		x							
Access type (fistula/graft/line)		x							
HD modality: (HD, HDF)		x							
Incremental/full start dialysis		x							
Transplant wait listed		x							
Dialysis prescription		x							
Bioimpedence with full dataset using software		x	x	x	x	x			x if indicated
BISTRO Study intervention record		x	x	x	x	x			x if indicated
Duke Activity Status Index (ASI)		x			x	x			
Patient Activation Measure (PAM)		x			x	x			
EQ-5D-5 L		x			x	x			
IPOS-Renal patient version		x			x	x			
Haemodialysis symptoms questionnaire		x			x	x			
Short Form (SF-12) Health Survey		x			x	x			
CSRI CKD		x			x	x			
Cognitive Assessment (MoCA)		x					x annually		
Study Termination/completion form								x	x
Adverse events									x

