#### Secondary outcomes

Difference in rate of decline in renal clearance will be analysed using a random slopes linear mixed model, with adjustment for baseline characteristics, as for the primary outcome. We will analyse the effect of randomization on fluid status and body composition as determined by BI (to ascertain the effect of the intervention on the fluid assessment decision) and undertake corresponding appropriate analyses of the other secondary outcomes such as (i) *dialysis-related symptoms and treatment efficacy* (e.g. inter-dialytic fluid gain, falls, post-dialysis recovery time), (ii) *critical events* such as cardiovascular events and interventions, access-related interventions/failures and death, and (iii) *patient-reported measures* (e.g. EQ-5D-5 L, SF-12, PAM, POS-S renal, CSRI CKD). In analysing the effect of the intervention on patient activation measures we will look to see if this is associated with objective measures of fluid management, e.g. inter-dialytic fluid gain which, following adjustment for comorbidity, is a surrogate measure of patient survival.

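### The primary model's covariate list leaves out baseline residual kidney function, which is already measured at Visit −1; this costs precision but not validity

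*Protocol article*

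**What the plan says.** Under Statistical methods, Primary outcome, the protocol article describes a competing-risks analysis reported as a sub-hazard ratio and states: "The analysis will control for known baseline covariates affecting residual function [26, 29], i.e. age, race, sex, comorbidities". The list ends with "antihypertensive drug use (ACE inhibitors/ARBs, calcium antagonists) and diuretic use". It is introduced by *i.e.*, so it reads as the full set rather than as examples.

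Other sections bear on the point:

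- **Outcomes:** anuria is a urine volume of at most 100 ml/day, or at most 200 ml in the short inter-dialytic period, confirmed by a repeat collection.
- **Eligibility criteria:** entry needs more than 500 ml (per day before dialysis starts, per short inter-dialytic period afterwards) or a clearance of at least 3. There is no upper limit.
- **Table 1:** the row "Residual kidney function tests for normalized GFR (urine volume and urine + blood to lab") is marked at Visit −1.
- **Allocation:** permuted blocks stratified by centre. Residual function is not a stratification factor.
- **Abstract and Discussion:** these add adjustment for patient characteristics in general and for unit practice patterns. Neither names residual function.

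**The concern.** The endpoint is the time for urine volume to fall to a fixed level, so the starting volume sets the distance to the event. A variable this close to the endpoint would normally come first on the covariate list. Here it is absent, although it is collected for eligibility and nothing in the design balances it.

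Two things are at stake. First, leaving a prognostic variable out of a hazard model pulls the estimated ratio towards 1 and lowers power for the same marginal difference in incidence. Second, if one arm happens to start with more urine output, that difference passes into the primary estimate. In an open-label trial, adding the covariate only after an imbalance has been seen would look data-driven, so the choice should be made in advance.

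**Working it through.** **1. The plan's own figures**

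Inputs from Sample size, Primary outcome:
- Rates: "cumulative 10-month incidence of anuria of 30% in the control group and 20% in the treatment group and 11% competing risks"
- Error rates: two-sided 5% level and 90% power, for which the plan states 185 events
- Timing: recruitment over one year, then one further year of observation
- Size: 516 patients in two equal arms, after an allowance of 5% for losses

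Constant cause-specific hazards per month:
- Control: −ln(1 − 0.41)/10 × 30/41 = 0.03861
- Treatment: −ln(1 − 0.31)/10 × 20/31 = 0.02394
- Hazard ratio: 0.02394/0.03861 = 0.620

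Schoenfeld events: 4 × (1.960 + 1.282)² / (ln 0.620)² = 184.02, rounded up to 185.

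Patients: with uniform accrual over 12 months and 12 further months of follow-up, the mean probability of an observed anuria event is 0.3777. Then 185/0.3777 = 489.7, and 489.7/0.95 = 515.5, rounded up to 516. Both stated figures are reproduced.

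**2. How far starting values can differ**

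At the two volume floors, patients enter at 500/100 = 5 times and 500/200 = 2.5 times their anuria threshold. If volume falls by a constant proportion each month (an assumption), the first takes ln 5/ln 2.5 = 1.76 times as long to reach it. Entry by clearance alone, and the lack of an upper limit, can widen the spread further.

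**3. Effect of adjustment on power**

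Simulation with 516 patients, the accrual and follow-up above and about 5% loss. The marginal 10-month anuria incidences were held at 30% and 20%, with 1,500 trials per scenario. Baseline function enters as one standardised variable. Its strength is **assumed**, because the documents give no figure.

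| Anuria HR per SD higher (lower) baseline | Fine-Gray power without | with | Cause-specific power without | with |
|---|---|---|---|---|
| 1 (1) | 89.1% | 89.4% | 91.0% | 90.9% |
| 0.8 (1.25) | 88.1% | 89.1% | 89.4% | 90.5% |
| 0.67 (1.5) | 88.3% | 90.0% | 89.3% | 91.4% |
| 0.5 (2.0) | 87.1% | 92.2% | 88.0% | 92.9% |
| 0.4 (2.5) | 84.4% | 93.4% | 86.1% | 95.3% |

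The Fine-Gray gains are 1.0, 1.7, 5.1 and 9.0 points. The simulation error of a single power figure is about √(0.9 × 0.1/1500) = 0.8 points. Within a row both models are fitted to the same simulated trials.

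A separate Fine-Gray simulation with 490 patients and no losses gave 86.5% v 88.9%, 84.7% v 89.5% and 83.1% v 92.2% at hazard ratios of 1.5, 2.0 and 2.5 per SD. Those are gains of 2.4, 4.8 and 9.1 points.

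**4. Type I error**

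With no treatment effect, rejection rates were 4.1% to 5.2% across both model types, with and without the covariate.

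**5. Chance imbalance**

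The standard error of a standardised mean difference is about 2/√516 = 0.088, so the 95% limit is 1.96 × 0.088 = 0.17 SD. An imbalance of that size shifts the unadjusted hazard ratio by a factor exp(|ln HR per SD| × 0.173): 1.04 at 0.8, 1.07 at 0.67, 1.13 at 0.5 and 1.17 at 0.4.

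**The case against.** The best defence is that the list is a summary. The Abstract and Discussion name adjusters that it omits, the form of the comorbidity term is left open, and the analysis is referred to a statistical analysis plan that is not shown. This carries some weight, since that plan may include baseline function. But the article makes a positive statement of the covariates affecting residual function, and none of its wider statements supplies the missing one. An analysis plan that follows the protocol would inherit the omission.

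Three further objections stand and limit the point:

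- **Validity.** A reader might infer that the primary result would be biased. It would not. Randomisation protects the test, and the error rate and confidence interval already allow for chance imbalance. The shift of the ratio towards 1 is the difference between a marginal and a conditional effect, and the 30% v 20% planning assumption is itself marginal.
- **Size.** The prognostic strength is assumed, and the simulations leave out the covariates that the plan does include. Diuretic use, age and comorbidity may carry part of the same information, which would shrink the gain. Nor is all of the shortfall from 90% due to the omission: Fine-Gray power is 89.1% even when baseline function has no prognostic value.
- **Slope outcome.** The secondary analysis is described as "with adjustment for baseline characteristics, as for the primary outcome", from which a reader might infer that the slope model ignores baseline function too. The documents do not support this. The sample-size text for that outcome counts an assessment at month 0, so starting clearance is already a response in the random-slopes model.

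**Conclusion.** The point holds for the primary model, as a loss of precision. The stated covariate list omits an already collected baseline value of the quantity that defines the endpoint, and stratification does not make up for it. Over an assumed hazard ratio of 1.25 to 2.5 per SD lower baseline function, adjustment is worth about 1 to 9 points of power. The upper end needs very strong prognosis, and overlap with the listed covariates would reduce the gain. A chance imbalance at the 95% limit would move the unadjusted hazard ratio by 4% to 17% over the same range.

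It might be tempting to conclude that the trial is undersized. The documents do not support that: 185 events and 516 patients follow from the stated assumptions. The change is well worth making, but the analysis is not invalid without it.

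**What to change.** Add to the pre-specified covariates of the primary model, from the Visit −1 collection:

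- continuous baseline urine volume, log-transformed and expressed per 24 h, and/or continuous baseline mean urea and creatinine clearance;
- an indicator for a 24-h collection before dialysis versus an inter-dialytic collection.

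The cost is small: a sentence in the protocol or analysis plan, one to three extra terms in a model planned for 185 events, and a rule for converting inter-dialytic volumes to a 24-h scale. Volume and clearance are probably correlated, so the plan should say whether one or both enter. No new data are needed and the sample size need not change. The addition should be dated before any comparison by arm is seen.

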#### Secondary outcomes

Difference in rate of decline in renal clearance will be analysed using a random slopes linear mixed model, with adjustment for baseline characteristics, as for the primary outcome. We will analyse the effect of randomization on fluid status and body composition as determined by BI (to ascertain the effect of the intervention on the fluid assessment decision) and undertake corresponding appropriate analyses of the other secondary outcomes such as (i) *dialysis-related symptoms and treatment efficacy* (e.g. inter-dialytic fluid gain, falls, post-dialysis recovery time), (ii) *critical events* such as cardiovascular events and interventions, access-related interventions/failures and death, and (iii) *patient-reported measures* (e.g. EQ-5D-5 L, SF-12, PAM, POS-S renal, CSRI CKD). In analysing the effect of the intervention on patient activation measures we will look to see if this is associated with objective measures of fluid management, e.g. inter-dialytic fluid gain which, following adjustment for comorbidity, is a surrogate measure of patient survival.

